## Abstract

**Introduction::**

Conducting neoadjuvant chemoradiotherapy (CRT) and additional preoperative consolidating chemotherapy (CTx), that is, total neoadjuvant therapy (TNT), improves local control and complete response (CR) rates in locally advanced rectal cancer (LARC), putting the focus on organ preservation concepts. Therefore, assessing response before surgery is crucial. Some LARC patients would either not benefit from intensification by TNT or may reach CR, making resection not mandatory. Treatment of LARC should therefore be based on patient individual risk and response to avoid overtreatment.

The “PRIMO” pilot study aims to determine early response assessment to form a basis for development and validation of a noninvasive response prediction model by a subsequent prospective multicenter trial, which is highly needed for individual, response-driven therapy adaptions.

**Methods::**

PRIMO is a prospective observational cohort study including adult patients with LARC receiving neoadjuvant CRT. At least 4 multiparametric magnetic resonance imaging (MRI) scans (diffusion-weighted imaging [DWI] and hypoxia-sensitive sequences) as well as repeated blood samples in order to analyze circulating tumor cells (CTC) and cell-free tumor DNA (ctDNA) are scheduled. Pelvic radiotherapy (RT, 50.4 Gy) will be performed in combination with a 5-fluorouracil/oxaliplatin regimen in all patients (planned: N = 50), succeeded by consolidation CTx (FOLFOX4) if feasible. Additional (immuno)histochemical markers, such as tumor-infiltrating lymphocytes (TIL) and programmed death ligand 1 (PD-L1) status will be analyzed before and after CRT. Routine resection is scheduled subsequently, nonoperative management is offered alternatively in case of clinical CR (cCR).The primary endpoint is pathological response; secondary endpoints comprise longitudinal changes in MRI as well as in CTCs and TIL. These are evaluated for early response prediction during neoadjuvant therapy, in order to develop a noninvasive response prediction model for subsequent analyses.

**Discussion::**

Early response assessment is the key in differentiating “good” and “bad” responders during neoadjuvant CRT, allowing adaption of subsequent therapies (additional consolidating CTx, organ preservation). This study will contribute in this regard, by advancing MR imaging and substantiating new surrogate markers. Adaptive treatment strategies might build on these results in further studies.

## 1. Introduction

Locally advanced rectal cancer (LARC), comprising Union Internationale Contre Le Cancer stage II and III cancers, has been treated routinely with preoperative (chemo)radiotherapy (RT) and subsequent resection. Optionally, adjuvant chemotherapy (CTx) was advised in case of postoperative risk factors (such as positive resected lymph nodes). This treatment schedule has been standard for over 15 years, resulting in pathological CR (pCR) rates in the range of 10%.^[1]^ Habr-Gama et al hypothesized even before, that patients achieving pCR after preoperative treatment, would have similar long-term outcomes if no resection would be performed.^[2]^ Up to now, several study groups around the world are searching for adequate treatment schedules to establish this “watch and wait” concept in cases of complete response (CR) after neoadjuvant chemoradiotherapy (CRT).

Different approaches have been investigated, favoring an intensification of preoperative treatment by consolidating CTx after initial CRT. Several European trial groups were able to demonstrate increased pCR rates over 50% and increased local tumor control rates by this additional preoperative CTx,^[3–6]^ evolving the so-called “total neoadjuvant therapy” (TNT) regime. This regime, consisting of pelvis RT, for example, with concomitant fluoropyrimidine-based CTx, and followed by consolidating fluoropyrimidine-based CTx, is currently recommended by the German expert associations (Arbeitsgemeinschaft Radiologische Onkologie of DKG [Radiation Oncology working group German Cancer Society] [ARO], Arbeitsgemeinschaft Internistische Onkologie of DKG [Medical Oncology working group of German Cancer Society], Arbeitsgemeinschaft Chirurgische Onkologie of DKG [Surgical Oncology working group German Cancer Society]) for LARC.^[7]^

Based on these promising results, current studies are investigating “*watch and wait*” concepts for those patients responding well to CRT. The recently presented ARO-16 trial was able to demonstrate that 40% of the patients were eligible for resection-free treatment.^[8]^ It hence seems that patients with good tumor regression after surgery could be offered a “*watch and wait*” concept, potentially avoiding resection and increasing quality of life (QoL).

On the other hand, there is a substantial group of patients not reaching pCR after neoadjuvant treatment, so that a resection would still be necessary. Additional preoperative CTx might be considered as ineffective in case of inevitable resection for this group.^[9]^ Deciding if there is an additional benefit when performing preoperative CTx is relevant due to a possible increase of toxicity, like polyneuropathy.^[5]^

Accurate tumor response assessment is the key to allow substantiated decisions whom to offer “*watch and wait*” or not. Even more, early response prediction during neoadjuvant CRT would allow adapting the following treatment, that is, additional CTx to maximize tumor regression in order to obtain pCR versus a straight resection schedule to evade additional toxicity if no pCR is probable. However, differentiating “good responders” and “bad responders” by single clinical examinations only does not seem sufficiently reliable^[10]^ and, to our information, there is no reliable model to anticipate response and benefit from TNT respectively.

Valentini et al^[11]^ were already providing nomograms to estimate tumor control and survival rates based on retrospective analysis. Based on this work, the so-called Neoadjuvant Rectal Score (NAR) was derived, serving as easy-to-apply surrogate for clinical endpoints.^[12,13]^ But to our knowledge, no validated tool based on TNM staging for early response assessment during neoadjuvant treatment has been published up to now.

In this trial, we aim to combine different diagnostic modalities in order to combine them for response assessment in a multimodal cluster. The 3 columns are described subsequently.

One column comprises multiparametric magnetic resonance imaging (MRI), focusing mainly on diffusion-weighted imaging (DWI) and hypoxia-sensitive susceptibility sequences (T2*) in addition to standard T2-weighted images. Both DWI and T2* were established for tumor imaging as they yield information about impaired cell integrity or microenvironment.^[10,14–16]^ There have been promising results published for DWI imaging for rectal cancer diagnosis^[15,16]^; however, there is no reliable option to predict tumor regression by single pre- or post-treatment apparent diffusion coefficient values up to now.^[17]^ Our concept is to establish robust longitudinal assessment in order to extrapolate signal trends, as it is successfully performed with serum tumor markers (carcinoembryonic antigen, CA19-9). T2* on the other hand has recently been investigated in other tumor sites, such as head and neck malignancies.^[18,19]^ At these sites, T2* imaging seems to enable microenvironment evaluation (angiogenesis, hypoxia). However, there is no common use for T2* in rectal cancer. Considering hypoxia is crucial for radiobiological reasons, as hypoxic tissue is one of the key points for radiation resistance. Thus, an association to bad response is probable. Interleukin 6 may serve as surrogate for hypoxia dynamics^[20]^ and will therefore be of interest in this trial.

Tumor environment is also characterized by local tumor-infiltrating lymphocytes (TILs). For example, these are approved as independent prognostic factor in breast cancer.^[21,22]^ But currently there is no standard use in rectal cancer.^[23]^ Consequently, we aim to analyze pre- and post-treatment specimens of TILs and surface antigens (CD3, CD4, CD8, and CD45) and to correlate treatment-related changes with tumor regression as second column.

Further longitudinal trends will serve as third column. We plan to perform liquid biopsies longitudinally in order to detect therapy-induced changes of circulating tumor cells (CTCs) and cell-free tumor DNA (ctDNA). Both are proofed as surrogate markers in other malignancies, but their role in response assessment of rectal cancer remains still unclear.^[24–26]^ Longitudinal trends could serve as surrogate for therapy response.^[25]^ Additionally, we focus on treatment-related changes of surface proteins (e.g., programmed death ligand 1 [PD-L1]). Detection of CTCs or ctDNA may be investigated postoperatively for its significance in relapse diagnostics.^[24]^

The PRIMO trial serves as pilot trial to hypothesize a noninvasive response prediction model, which will be tested and validated in a larger subsequent multicenter study. Secondly, the earliest time point for response estimation should be identified and be then validated in the subsequent trial, in order to allow differentiation between “good responders” and “bad responders” as early as possible during neoadjuvant therapy.

## 2. Material and methods

### 2.1. Design

This trial, entitled “*Planning Adaptive Treatment by Longitudinal Response Assessment Implementing MR Imaging, Liquid Biopsy and Analysis of Microenvironment during Neoadjuvant Treatment of Rectal Cancer*” (*PRIMO*), is a monocentric observational pilot cohort study (Fig. 1) to be conducted at Jena University Hospital (Jena, Germany). The trial protocol (current version 1.2, 2023-03-01) is structured on the basis of the *Standard Protocol Items: Recommendations for Interventional Trials* guidelines^[27]^ and conforms to the international *Consolidated Standards of Reporting Trials* guidelines.^[28]^ It is additionally provided in this work (Supplemental Digital Content 1, http://links.lww.com/MD/I827). The implementation and reporting of the trial follows the principles of *Good Clinical Practice*^[29]^; this trial was registered at clinicaltrials.gov (ID: NCT05524012) prior to recruitment.

**Figure 1. F1:**
[figure not shown]
A graphical abstract, summarizing the trial design and scheduled interventions of the PRIMO trial: In this observational pilot study, we aim to analyze N = 50 patients with Locally Advanced Rectal Cancer (LARC) by longitudinal diagnostics in order to develop early noninvasive response assessment models.

Patients with LARC, defined as Union Internationale Contre Le Cancer Stage II/III cancer, are eligible for this trial. We aim to enroll N = 50 patients (Table 1). These patients are subjected to a neoadjuvant CRT, which is international standard of care. Each patient will be followed-up for 5 years.

**Table 1 T1:** Inclusion criteria for the PRIMO trial.

Inclusion criteria	
LARC, UICC stage II/III	Each T4 tumor; Each T3 tumor when located distally (0–6 cm) T3 and location >6 cm: in case of risk factors (e.g., N+, EMVI+, MSP+, >cT3b)
Sufficient liver/renal function; No severe cytopenia	GFR > 45 mL/min; liver enzymes < 2.5 ULN Neutrophils ≥ 3 × 10^9^/l; Thrombocytes ≥ 100 × 10^9^/l; Hemoglobin ≥ 6 mmol/l
No contraindications for MRI	Incompatible endoprosthesis/cardiac devices; severe claustrophobia; severe adipositas (BMI > 30 kg/m^2^)
No further relevant secondary diagnosis	No homozygous DPD-deficiency; No severe cardiac disease No severe pulmonary disease No severe psychologic disorder For female patients: No pregnancy. No history of preceding chemo(radio)therapy or parallel participation in other clinical trials.

BMI = body mass index, EMVI = extramural vascular invasion, GFR = glomerular filtration rate, MRI = magnetic resonance imaging, MSP+ = infiltration of Mesorectal Plane, N+ = positive lymphnodes, UICC = *Union Internationale Contre Le Cancer*, ULN = upper limit of normal range.

Pretreatment tumor specimens and resection or biopsy specimens after neoadjuvant treatment will be appraised by 1 single expert pathologist (NG) in order to classify the tumor regression grading (TRG), according to Werner/Hoefler,^[30,31]^ and to perform secondary assessments of TILs and their surface antigen cluster (CD3+, CD4+, CD8+, CD45+). By pre- and post-treatment tumor grading, the established NAR by George et al^[12,32]^ will be calculated for secondary comparison. Furthermore, pre- and post-treatment expression of surface proteins (like PD-L1) will be compared. We require 5 serial biopsies if nonoperative management is performed.

Multimodal longitudinal assessments are scheduled during neoadjuvant treatment. These comprise especially multiparametric MRI scans of the rectum to quantify tumor regression, including noncontrast enhanced T2-weighted imaging as well as additional DWI- and hypoxia-sensitive T2*-sequences. Four to 6 MRI scans are scheduled, depending if “TNT” would be indicated (Fig. 2). Radiological features of all sequences are obtained longitudinally from 3 regions of interest within the tumor area as well as a region of interest placed in unaffected rectum within the radiation field for comparison purposes. Each will be positioned consent-based by 2 radiotherapists and, additionally, by a semiautomatic, cluster-based approach.

**Figure 2. F2:**
[figure not shown]
Workflow during the PRIMO trial until primary endpoint: All patients are receiving chemoradiotherapy, followed by either consolidation chemotherapy (total neoadjuvant therapy, TNT) or an 8-wk therapy free interval. During this 2-phase therapy, repeated MRI scans and liquid biopsies (circulating tumor cells, CTCs) are performed. A baseline of histology and tumor-infiltrating lymphocytes (TILs) is compared with resection or biopsy specimens after therapy. Overall duration is 34 wk (complete TNT) or 16 wk (no consolidation chemotherapy), respectively. MRI = magnetic resonance imaging.

Liquid biopsies, comprising CTCs and ctDNA, will be performed from routine blood samples regularly during neoadjuvant therapy and follow-up in addition to routine blood samples. These comprise C-reactive protein, interleukin 6 and carcinoembryonic antigen as well as standard blood counts, liver enzymes and creatinine. ctDNA will be investigated for somatic mutations, such as KRAS p.G12D/p.G12V/p.G13D or BRAF V600E, by sequencing. CTC analyses will be performed by fluorescence microscopy, focusing on EpCAM and further antigen detection (e.g., PD-L1). Measurement of the CTCs and ctDNA is planned regularly during preoperative treatment as well as annually during follow-up for 5 years.

QoL will be repeatedly measured applying EORTC QLQ-C30 v3.0^[33,34]^ and CR-29^[35]^ questionnaires during neoadjuvant treatment and follow-up. A detailed overview of the assessments and study procedures according to the *Standard Protocol Items: Recommendations for Interventional Trials* guideline is attached as Supplemental Digital Content 2, http://links.lww.com/MD/I828.

The REDCap electronic data capture tools^[36,37]^ will be used for data collection and management, ensuring compliance to local data privacy restrictions and promoting data quality. A professional clinical trial manager ([name]) manages trial conduction and will perform data curation and quality checks.

### 2.2. Treatment description

Informed consent of each patient is required for study participation. CRT is then conducted in a 2-phase design (Fig. 2). It consists of standard pelvis RT (50.4 Gy) and, if necessary, inguinal RT (45.0 Gy; involved groin nodes or distal tumor infiltration) in combination with 2 cycles of concomitant CTx (5-fluorouracil, plus oxaliplatin, once every 2 weeks - q2w).

In the second phase, additional consolidating CTx (9 cycles FOLFOX4, q2w) is advised for all patients in case of additional risk factors (as specified in Table 1: positive lymph nodes, infiltration of the mesorectal plane or extramural vessel invasion, distal tumor location or T4 tumors) and good tolerability of primary neoadjuvant CRT, according to current therapy recommendations of the German colorectal tumor expert associations (ARO, *Arbeitsgemeinschaft Internistische Onkologie* of DKG [Medical Oncology working group of German Cancer Society], *Arbeitsgemeinschaft Chirurgische Onkologie* of DKG [Surgical Oncology working group German Cancer Society]).^[7]^ This regime is also known as “Total Neoadjuvant Therapy” (TNT). Dose reduction of scheduled CTx in case of toxicity and adverse events, such as hemotoxicity and neuropathy, will be realized following the prescribing information. Depending on restaging results, resection is performed after 34 weeks or patients are offered a “*watch and wait*” approach in case of CR and good compliance.

In case of high toxicity (>CTC° III) or noncompliance during simultaneous CRT, a rectum resection is scheduled 8 weeks after completion of RT (week 16). Performing this 2-phase design allows adaption to individual patient consent and tolerability during ongoing therapy. Simultaneously, it ensures adequate treatment intensity even if no additional CTx would be realizable, as this group is still receiving a neoadjuvant therapy analogous to the approved ARO-04-protocol.^[1]^ We are conducting this 2-phased design (Fig. 2) for over 2 years as local standard at our institution.

### 2.3. Endpoints

The primary endpoint is defined as the tumor regression after neoadjuvant CRT and will be evaluated at week 16 or 34 respectively, depending on consolidating CTx. It will be quantified by a TRG according to Werner/Hoefler^[30]^ in resection or biopsy specimens, depending if nonoperative management was conducted. TRG 1a/b or 2 is considered as response (see Table 2). CR will be evaluated as secondary endpoint and is defined as a TRG 1a/b. Further secondary endpoints (Table 3) comprise correlation of radiological features to TRG and NAR^[12,32]^ as well as the correlation of longitudinal changes of CTCs/ctDNA and TILs to TRG, respectively. Therapy-related side effects (according to EORTC-CTCAE) and QoL (based on QLQ-C30 and CR-29 questionnaires) are secondary objectives, as well as 5-years progression free survival and overall survival after 5 years. Relapses occurring within the follow-up period serve as endpoint for ctDNA and CTC analyses regarding early diagnosis.

**Table 2 T2:** Tumor regression grading (TRG) according to Werner and Höfler^[30]^ and Becker et al^[31]^ TRG 1a/b is considered as complete response (cR).

Tumor regression grading according to Becker et al		
1a	Complete response (CR)	No vital tumor cells detectable
1b	Subtotal response (SR)	<10% vital tumor cells
2	Partial response (PR)	10%–50% vital tumor cells
3	Minimale response (MR)	>50% vital tumor cells
	No response (NR)	No histological evidence of regression

**Table 3 T3:** Primary and secondary endpoints of the PRIMO trial.

Endpoints	
Primary endpoint	Response rate according to tumor regression grading (TRG)-score/ypTNM
Secondary endpoints	Longitudinal changes in MRI during neoadjuvant treatment
	Presence/longitudinal phenotypic changes of ctDNA and CTC
	Presence/phenotypic changes of tumor-infiltrating lymphocytes (TILs)
	Surrogates of inflammation (CrP, IL-6) and tumor markers (CEA)
	Treatment-related toxicity (EORTC-CTCAE v5.0)
	Overall survival (OS), progression free survival (PFS), recurrence rate
	Quality of life (QoL) according to EORTC QLQ-C30 and QLQ-CR29

Tiered analyzes is planned, evaluating endpoints referencing to neoadjuvant treatment when enrolled patients have met the primary endpoint and analyzing secondary endpoints referring to follow-up results after 5 years follow-up.

CEA = carcinoembryonic antigen, CRP = C-reactive protein, CTC = circulating tumor cell, ctDNA = cell-free tumor DNA, IL-6 = interleukin 6, MRI = magnetic resonance imaging.

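### The secondary endpoint CR pools TRG 1a and 1b, although Table 2 reserves complete response for 1a, so the reported CR rate will exceed the table's own CR rate by the share of patients graded 1b

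*Protocol article*

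**What the plan says.** Three statements in the protocol article, section 2.3 Endpoints, bear on the point.

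- The text on secondary endpoints: "CR will be evaluated as secondary endpoint and is defined as a TRG 1a/b".
- The caption of Table 2: "TRG 1a/b is considered as complete response (cR").
- The rows of Table 2. Grade 1a is labelled complete response, with the criterion "No vital tumor cells detectable". Grade 1b carries its own label, "Subtotal response (SR"), with the criterion "<10% vital tumor cells".

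Response for the primary endpoint is wider: "TRG 1a/b or 2 is considered as response (see Table 2").

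The Introduction cites pathological complete response rates in the region of 10% under the older standard and above 50% with added preoperative chemotherapy. It also gives the hypothesis behind organ preservation, that "patients achieving pCR after preoperative treatment, would have similar long-term outcomes if no resection would be performed".

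**The concern.** The label CR has two meanings within one section. A patient graded 1b is a complete responder by the text and the caption, and a subtotal responder by the table row. The article does not explain the pooling and does not say that grade 1a will be reported on its own.

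What is at stake is how one secondary rate is read. CR is the histological endpoint closest to the organ-preservation rationale, and the Introduction frames that rationale through pCR rates. Someone who sees a CR rate from this trial will naturally set it beside those figures. With 1b included, the two are different quantities, and the difference always makes the trial's rate look better.

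**Working it through.** **1. The plan's own figures, and whether they depend on the CR definition.** Section 2.4 gives detectable AUCs of about 0.76 (n = 35) and 0.72 (n = 50), with power 0.80, two-sided alpha 0.05 and 60% responders. Taking 60% in both samples, the check tests one AUC against 0.5:

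power = Φ( (AUC − 0.5 − 1.96·√V0) / √V1 )

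V0 and V1 are the variances of the estimated AUC at 0.5 and at the alternative, with the Obuchowski binormal form

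V = 0.0099·exp(−A²/2)·[(5A² + 8) + (A² + 8)/k] / n1, where A = 1.414·Φ⁻¹(AUC) and k = n0/n1.

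- n = 35: n1 = 21, n0 = 14. Power 0.80 is reached at AUC 0.763.
- n = 50: n1 = 30, n0 = 20. Power 0.80 is reached at AUC 0.723.

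The Hanley-McNeil variance gives 0.765 and 0.725. The stated values are reproduced. They rest on response as TRG 1a, 1b or 2, so moving 1b out of CR leaves n1, n0 and both AUCs unchanged.

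**2. The definitions side by side.**

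| Grade | Criterion (Table 2 row) | Label in row | CR by row? | CR by text and caption? | Primary response? |
|---|---|---|---|---|---|
| 1a | no vital tumour cells | complete | yes | yes | yes |
| 1b | below 10% vital cells | subtotal | no | yes | yes |
| 2 | 10% to 50% vital cells | partial | no | no | yes |
| 3 | above 50% vital cells | minimal | no | no | no |

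Only the 1b row is in conflict, and only for CR.

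**3. Size of the discrepancy.** Let p1a and p1b be the shares of patients in each grade.

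- CR rate by text and caption: p1a + p1b
- CR rate by table row: p1a
- Difference: p1b
- Share of patients labelled CR who have vital tumour: p1b / (p1a + p1b)

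The article gives neither p1a nor p1b for this trial. As an assumption, let each lie between 10% and 30%. The largest combination, 30% + 30% = 60%, equals the expected response rate and so is still compatible with it.

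- Patients counted as CR with vital tumour, N = 50: 0.10 × 50 = 5 to 0.30 × 50 = 15.
- The same for N = 35: 0.10 × 35 = 3.5 to 0.30 × 35 = 10.5.
- Lowest share among CR: 0.10 / (0.30 + 0.10) = 25%.
- Highest share among CR: 0.30 / (0.10 + 0.30) = 75%.
- With both grades at 10%, the reported CR rate would be 20% against 10% by the table row.

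The direction does not depend on the assumption: the pooled rate is higher whenever any patient is graded 1b. The size depends on it entirely.

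**The case against.** The best defence is that the pooling is deliberate and open. It stands in both the text and the caption, with the grade definitions next to it. A combined category of good regression is a legitimate endpoint. Grades are recorded individually, so the 1a rate can be recovered at any time. CR takes up one sentence among the secondary endpoints, is not a separate line in Table 3, and belongs to a pilot meant for estimation rather than testing. The article also announces no comparison of its CR rate with the cited pCR rates, and the Introduction mentions good tumour regression, not only pCR, as a possible basis for watch and wait.

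Most of this stands, and it limits the severity. It does not remove the conflict. Disclosing the grouping does not justify a name that the same table gives to a narrower category, and a rate called CR invites comparison with the pCR rates even if none is planned.

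Two stronger readings are tempting, and the article supports neither.

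- *A prediction model would be trained to call residual cancer complete.* The article describes no model for CR. The primary hypothesis in section 2.4 concerns response, which is TRG 1a/b/2, and the correlations in section 2.3 are with TRG and NAR.
- *Patients would be steered to nonoperative management on a flawed definition.* The Abstract ties that offer to clinical CR and section 2.2 ties it to restaging. Neither uses TRG 1a/b. The shared abbreviation may confuse, but no link to care is shown.

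**Conclusion.** The point holds as an inconsistent definition of one secondary endpoint. Followed as written, the histological CR rate exceeds the rate under the table's own label by exactly the 1b rate, and it is not comparable with the pCR rates in the Introduction. The comparability statement assumes that pCR there has its usual meaning of no residual vital tumour, since the article does not define it.

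The size is unknown. The figures of 5 to 15 of 50 patients, and 25% to 75% of those labelled CR, illustrate assumed grade shares and are not estimates for this trial. A reader might infer that the main analysis is compromised, but it is not: the primary endpoint, the expected 30 of 50 responders and the AUCs of 0.76 and 0.72 are the same under either definition. Severity: should be fixed.

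**What to change.** Reconcile the text of section 2.3, the caption of Table 2 and its rows before the endpoint analysis, so that the choice is not made with the grades in view. Either of two changes is enough:

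- define the histological CR endpoint as TRG 1a in the text and the caption, and report 1a+1b separately under another name, such as *complete or subtotal regression*; or
- keep the pooled endpoint under such a name, and report the 1a rate as CR.

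It would also help to state that this histological CR is distinct from the clinical CR judged at restaging. This concerns labelling and reporting only and asks for no change to patient management.

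The cost is one sentence and one caption. TRG is graded for every patient in any case, so no new data are needed. The price is a less favourable CR rate, lower by the 1b share.

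### The secondary endpoint complete response rests on the regression grade alone, so an operated patient with positive resected nodes can count as a complete responder

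*Protocol article*

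**What the plan says.** Section 2.3 (Endpoints) fixes complete response in one sentence: "CR will be evaluated as secondary endpoint and is defined as a TRG 1a/b". The Table 2 caption says the same: "TRG 1a/b is considered as complete response (cR". The grades in Table 2 are defined by residual vital tumour. Grade 1a is "No vital tumor cells detectable" and grade 1b is "<10% vital tumor cells". Nodes are not mentioned.

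Response for the primary endpoint is also given by grade alone in the text: "TRG 1a/b or 2 is considered as response (see Table 2". Table 3, however, labels the primary endpoint "Response rate according to tumor regression grading (TRG)-score/ypTNM". No rule says how ypTNM enters either response or CR.

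The grade is read on the resection specimen or, under nonoperative management, on biopsies.

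Two other places show that nodal disease matters in this population. Table 1 (section 2.1) admits "T3 and location >6 cm: in case of risk factors (e.g., N+, EMVI+, MSP+, >cT3b", and section 2.2 lists positive nodes among the factors for which consolidation is advised. The Introduction says that adjuvant chemotherapy was advised for "postoperative risk factors (such as positive resected lymph nodes".

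**The concern.** A complete response label should not cover a patient in whom the pathologist has found cancer in the resected nodes. The article's rule allows this, because it looks only at the regression grade. The information that would prevent it is already named in Table 3, and the Introduction treats positive resected nodes as a reason for further therapy.

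What is at stake is the reported CR rate, a secondary endpoint of a pilot meant to prepare a larger multicentre study. A rate that includes node-positive patients is too high, and the definition may be carried into that study.

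**Working it through.** **Step 1. Does the rule admit node-positive patients?** The article does not say whether the grade covers the primary tumour only or the whole resection specimen, so both readings are checked for an operated patient with positive nodes (ypN+).

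| Reading of the grade | Grade 1a with ypN+ possible? | Grade 1b with ypN+ possible? | Counts as CR? |
|---|---|---|---|
| Primary tumour only | Yes: primary cleared, nodes not graded | Yes | Yes, through 1a or 1b |
| Whole specimen | No: vital cells are present in the nodes | Yes, if vital cells are below 10% | Yes, through 1b |

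The rule admits such patients under either reading. The result covers operated ypN+ patients graded 1a or 1b. It does not cover every node-positive patient.

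**Step 2. Does any stated figure depend on CR?** Section 2.4 gives detectable AUCs of about 0.76 (n = 35) and 0.72 (n = 50) at power 0.80, two-sided 0.05, with 60% responders. A normal approximation against an AUC of 0.5, with separate null and alternative variances, gives 0.763 and 0.723 with the Obuchowski binormal variance. The Hanley-McNeil variance gives 0.765 and 0.725. The stated figures therefore reproduce. They refer to response as grade 1a/b/2, so the CR definition does not enter them.

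**Step 3. Size of the overstatement.** Let *p* be the share of the cohort graded 1a/b, *o* the share of those who are operated, and *f* the share of those operated who are ypN+. The overstatement of the CR rate is *p* × *o* × *f*.

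Inputs:
- Cohort sizes of 35 (expected complete consolidation) and 50 (all patients), from section 2.4.
- *p* = 0.40, an assumption. The figure is borrowed from the share eligible for resection-free treatment in another trial, cited in the Introduction. The article gives no CR rate for this trial.
- *o* = 1, an assumption that gives the largest effect.
- *f* = 0.05 to 0.15, an assumption with no source in the article.

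Results:
- n = 35: 0.40 × 35 = 14 CRs; 14 × 0.05 = 0.7 and 14 × 0.15 = 2.1 patients; 0.7/35 = 2% and 2.1/35 = 6%.
- n = 50: 0.40 × 50 = 20 CRs; 20 × 0.05 = 1 and 20 × 0.15 = 3 patients; 1/50 = 2% and 3/50 = 6%.

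**Step 4. Sensitivity.**
- If only half of the grade 1a/b patients were operated (*o* = 0.5), the range would be 0.40 × 0.5 × 0.05 = 1 to 0.40 × 0.5 × 0.15 = 3 percentage points.
- With 10 to 25 of 50 patients graded 1a/b, all operated, and *f* from 0.05 to 0.20, the number affected runs from 10 × 0.05 = 0.5 to 25 × 0.20 = 5 patients, or 1 to 10 percentage points.
- With 20 such patients, the CR rate falls from 40% to 38%, 36% or 32% at *f* = 0.05, 0.10 or 0.20.

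**The case against.** The strongest defence is that CR is a secondary endpoint of a pilot whose stated scope is estimation. The definition is explicit and the same in both places, and ypTNM is named, so CR by nodal status could be reported later without new data. That is fair and limits the weight of the point. It does not rescue the rule: this is not a detail left to the full protocol but a complete definition, stated twice, that gives the wrong label.

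Other parts of the defence stand, and they rule out stronger readings that a reader might infer:

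- *The label corrupts the marker analyses or shifts an AUC.* The article plans no AUC for CR and no scoring of markers against CR. Section 2.3 relates imaging features to the grade and the NAR score, and liquid-biopsy and lymphocyte changes to the grade. The only AUC statement concerns response.
- *The label decides who avoids resection.* In operated patients, the grade and the nodal result exist only after surgery. Nonoperative management is offered on clinical complete response at restaging.
- *A cleared primary with positive nodes is certainly grade 1a.* This holds only if the grade describes the primary tumour alone, which the article does not say. Under the whole-specimen reading the problem arises through 1b.
- *The 2 to 6 points are an estimate for this trial.* They are not. The 40% is another trial's eligibility share, and taking all patients as operated gives the largest effect for the assumed shares.
- *A nodal rule would leave only tumour-free patients in CR.* It would not while grade 1b, which Table 2 itself calls subtotal response, counts as CR.

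**Conclusion.** The point holds in a limited form. The CR definition in section 2.3 and the Table 2 caption lets operated patients with positive resected nodes count as complete responders, and the article does not reconcile this with ypTNM in Table 3. The effect is an overstated CR rate.

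Under the assumptions shown (40% grade 1a/b, all operated, 5% to 15% node-positive) it is about 2 to 6 percentage points, or one to three patients in 50. It shrinks in proportion as more of these patients are managed nonoperatively. None of the three inputs is a figure the article gives for this trial, so the size is illustrative. That the rule admits such patients needs no assumption. The definition should be corrected, but the stated sample size and AUC figures are untouched.

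**What to change.** - In section 2.3 and the Table 2 caption, require ypN0 in addition to the regression grade for CR in operated patients.
- Leave the regression grade unchanged as the measure of tumour regression.
- Report how many patients the nodal rule reclassifies.
- Report CR in nonoperated patients separately, labelled as without nodal confirmation, since biopsies yield no ypN.
- Reconcile the text with Table 3: say how ypTNM enters response and CR, or remove it from the primary endpoint label.

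The cost is one definition line and a small addition to the results. Nodal status is already named in Table 3, and no visit, sample or sample size changes. The reported CR rate will be slightly lower, and CR will mean something different in operated and nonoperated patients, which is why the two should be shown apart. Whether grade 1b belongs in CR has to be settled separately.
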